## Abstract

**Background:**

Although the painful shoulder is one of the most common dysfunctions of the locomotor apparatus, and is frequently treated both at primary healthcare centres and by specialists, little evidence has been reported to support or refute the effectiveness of the treatments most commonly applied. According to the bibliography reviewed, physiotherapy, which is the most common action taken to alleviate this problem, has not yet been proven to be effective, because of the small size of sample groups and the lack of methodological rigor in the papers published on the subject. No reviews have been made to assess the effectiveness of acupuncture in treating this complaint, but in recent years controlled randomised studies have been made and these demonstrate an increasing use of acupuncture to treat pathologies of the soft tissues of the shoulder. In this study, we seek to evaluate the effectiveness of physiotherapy applied jointly with acupuncture, compared with physiotherapy applied with a TENS-placebo, in the treatment of painful shoulder caused by subacromial syndrome (rotator cuff tendinitis and subacromial bursitis).

**Methods/design:**

Randomised controlled multicentre study with blind evaluation by an independent observer and blind, independent analysis. A study will be made of 465 patients referred to the rehabilitation services at participating healthcare centres, belonging to the regional public health systems of Andalusia and Murcia, these patients presenting symptoms of painful shoulder and a diagnosis of subacromial syndrome (rotator cuff tendinitis and subacromial bursitis). The patients will be randomised into two groups: 1) experimental (acupuncture + physiotherapy); 2) control (TENS-placebo + physiotherapy); the administration of rescue medication will also be allowed. The treatment period will have a duration of three weeks. The main result variable will be the change produced on Constant's Shoulder Function Assessment (SFA) Scale; as secondary variables, we will record the changes in diurnal pain intensity on a visual analogue scale (VAS), nocturnal pain intensity on the VAS, doses of non-steroid anti-inflammatory drugs (NSAIDs) taken during the study period, credibility scale for the treatment, degree of improvement perceived by the patient and degree of improvement perceived by the evaluator. A follow up examination will be made at 3, 6 and 12 months after the study period has ended. Two types of population will be considered for analysis: per protocol and per intention to treat.

**Discussion:**

The discussion will take into account the limitations of the study, together with considerations such as the choice of a simple, safe method to treat this shoulder complaint, the choice of the control group, and the blinding of the patients, evaluators and those responsible for carrying out the final analysis.

## Background

Painful shoulder is one of the most common complaints affecting the locomotor apparatus, and is frequently attended both at primary healthcare centres and by specialists. The annual incidence at primary healthcare centres is 1.2% [1,2]. This pathology, which becomes more common with age [3] and with the practice of certain occupations and sports, is evidenced mainly by pain, restricted movement and strength and by the loss of shoulder functionality. The incidence on occupational invalidity, though mentioned by most authors, remains unknown; only approximate data are available, such as those provided by *Instituto de Biomecánica *at Valencia, which has estimated that 50% of sick leave is accounted for by muscle or bone injuries in the shoulder or neck.

The most common actions taken at present to relieve the symptoms of painful shoulder include steroid injections, physiotherapy, oral NSAIDs and "wait and see"; hardly any of these measures have been tested scientifically to demonstrate their effectiveness in this situation [4]. According to the bibliography reviewed, physiotherapy, which is the most common treatment applied in this case, has not been conclusively shown to be effective; sample sizes have been small and methodological rigor lacking from the papers published in this respect. On the other hand, solid evidence has been produced that ultrasound therapy is ineffective in treating the painful shoulder [1,5,6].

The most relevant bibliography we have examined comprises reviews of the question carried out by the Cochrane group in 2000, 2003 and 2004, together with certain systematic reviews by other authors. In general, the conclusions of the analysts in the Cochrane studies, and of other reviewers working for professional organisations, is that there is very little evidence to support or refute the effectiveness of the treatment commonly applied for the painful shoulder. Therefore, well-designed studies are necessary, using uniform methods of diagnosis and measurement to ensure the validity of the results obtained. We have also analysed other studies, with less backing than the above-mentioned opinions of expert reviewers, but with an acceptable methodology, that have concluded in favour of one or other mode of treatment, such as physiotherapy [7,8] or the injection of corticoids [9,10]. We have also examined the recommendations of panels of experts and members of associations of physiotherapists and GPs.

Acupuncture has been used to treat this type of medical problem in China for over 3000 years. At present, it is under consideration as a technique to be applied in Western medical practice for a great many complaints, especially for cases in which modern techniques are either of limited effectiveness or are unsuitable [11]. Acupuncture is now widely used in the treatment of chronic pain [12-14]. The systematic review carried out by Lewith & Machin on the effectiveness of acupuncture in treating chronic pain concluded that treatment with "real" acupuncture was significantly more effective than that with "false" acupuncture and with a placebo [15]. It has also been shown that acupuncture provokes fewer adverse side effects than does the use of NSAIDs or opiates [16]. In recent years, randomised controlled studies have provided further evidence supporting the use of acupuncture in the treatment of pathologies of the soft tissues of the shoulder. For example, Kleinhenz et al. [17] observed an improvement of 19.2 points on Constant's scale for an experimental group versus one of 8.37 points among a control group, using a placebo featuring retractable needles, but these authors seem to have focused more on demonstrating the effectiveness of the technique used with the control group than on the specificity of the selection of the acupuncture points; moreover, with respect to the analysis of the main result variable (the absolute improvement achieved), the fit to the baseline measurement was not made. On the other hand, Sun et al. [18] (did aim to locate the specificity of the points, by selecting a point that was distal from the affected area, using a randomised controlled test with two groups; 13 patients were treated with acupuncture and specific exercises for the shoulder, and another 22 patients were treated solely with exercise. The design of the latter study is similar to that presented in this project although we believe the sample size is too small and a significant degree of bias was introduced by the fact that the control group (which received only exercises) did not receive the same medical attention as the experimental group. Nevertheless, the results obtained with the experimental group were significantly better than those of the control group. A further problem is that the point proposed by the authors (Zhongpin of the leg) is difficult to locate, as its situation is not constant, on the contrary to that of Tiaokou (ST38), which is situated exactly 8 cun below the articular line of the knee and 1 cun lateral from the tibial crest. Another clinical trial was reported by Gilbertson et al. [19], who described a case in which, after an arthroscopic intervention on the shoulder, traditional and sham acupuncture were compared. It was concluded that real acupuncture provides a significant improvement, concerning the degree of analgesia achieved, the reduction in the quantity of analgesics required, increased mobility and patient satisfaction; however, the acupuncture points selected are not described and so the trial is not reproducible.

Since the introduction of acupuncture techniques into primary healthcare at the *Dos Hermanas "A" *Health Centre, with the establishment of the Pain Treatment Unit, data have been compiled to obtain an initial evaluation of the reactions of patients who are given acupuncture treatment [20]. Moreover, a pilot study has been carried out to assess the immediate effects of this technique when applied to cases of supraspinal tendinitis [21] as a previous step to the development of the present study.

In this article, we describe a randomised, blinded, multicentre study carried out with a sufficiently-large sample group, with systematised, uniform diagnostic criteria, homogeneous therapeutic interventions including the use of a placebo for the control group, follow up periods exceeding three months and validated measurement of results. We believe such a systematic approach is necessary to clearly describe the current context of treatment for the painful shoulder. In the study, we work on the hypothesis that the acupuncture of Tiaokou ST38, together with physiotherapy, can reduce pain and improve functionality in situations of subacromial syndrome (rotator cuff tendinitis and subacromial bursitis) to a greater extent than does physiotherapy associated with a TENS-placebo treatment. The study began in March 2005 and the recruitment phase remains open.

## Methods/design

### Design

Randomised controlled multicentre study with blind evaluation by an independent observer and blind, independent analysis.

### Study subjects

Patients referred to the Rehabilitation services of the health centres participating in the study. These centres are part of the public health systems of the regions of Andalusia and Murcia (Spain). The patients presented chronic symptoms of subacromial syndrome (rotator cuff tendinitis and subacromial bursitis) and were offered treatment with physiotherapy together with acupuncture or transcutaneous stimulus. They were informed of the characteristics of the study and of the techniques to be used, as well as of the possible risks (infection, lipothymia, hematomas). They were told they could leave the study at any moment, with no type of penalisation or loss of benefits to which they were entitled.

### Selection criteria

Inclusion criteria

• Patients with a clinical diagnosis of subacromial syndrome (rotator cuff tendinitis and subacromial bursitis) with a case history > 3 months

• Prior radiography, with normal results

• Informed consent

• Unilateral injury

Exclusion criteria: surgery, luxations or fractures in the proximity of the shoulder; other severe direct or indirect traumas (in traction) observed in the anamnesis and clearly related to the onset of the current episode; hypocoagulates, generalised disorders of the musculoskeletal system or neurologic disorders, vascular trophic disorders in the lower limbs, lymphedema.

### Ethical criteria

The ethical validity of this study has been analysed and approved by the corresponding ethical and research committees at the healthcare centres involved. The study design takes into account the Principalism criteria of Beauchamp & Childress (beneficence, non-maleficence, autonomy and justice) and expressly guarantees the patient's right to privacy and informed decision-making. The study also complies with the norms for Good Clinical Practice and the Edinburgh 2000 revision of the Helsinki Declaration. All the patients who participate give their written, informed consent to the clinical research methods applied. During the development of the study, audits will be performed, according to the criteria of the Research and Ethics Committee and the healthcare centre's Quality Committee, independently of the external audits (research funding provider) that may be required.

### Criteria and procedures for withdrawal from the study

A patient may be withdrawn from the study at any time, either at will or by decision of the researcher. The reasons for interrupting participation in the study will be recorded on the summary page of the Digital Data Record (DDR). The following procedure is to be followed when a patient withdraws from the study:

• Assess the relevant study variables

• Record any adverse events

• Evaluate the taking of rescue medication

• Indicate the possible co-interventions carried out

• Complete the DDR, record the date and reason for withdrawal.

### Randomisation

The patients will be assigned on a random basis to the two study groups: 1) experimental group treated with acupuncture plus physiotherapy; 2) control group, to be given the TENS placebo plus physiotherapy. Randomisation will be carried out in each digital data recording system. Every healthcare centre participating in the study has a specially-designed DDR based on a Dell Axim × 30 PDA; once a new patient's data are entered, the patient is randomly assigned a treatment code (A = experimental; B = control). This code is concealed from the evaluator. Each PDA system has three access codes, one for the study controller, one for the evaluator and one for the doctor carrying out the treatment, and only the latter has access to the treatment code. The research team will take the necessary measures to ensure the confidentiality of the patients taking part, including their deidentification within the databases constructed for the analysis.

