### Data collection and analysis

Data collection and recording will be carried out using an Dell Axim × 30 PDA, fitted with the Windows^® ^operating system, and specially designed for the purposes of this study, with obligatory fields, validation rules and quality control for error avoidance; a 512 bit encoding system is incorporated to ensure the confidentiality of all the records. Furthermore, as additional functions, it will include a security analysis system with stored passwords, and functions for the export/import and synchronisation of the database content. Access to this PDA will be limited to THREE users: 1) the healthcare centre evaluator; 2) the doctor applying the treatments; 3) the study controller. Each will have a different access code.

The data tables describing the characteristics of the study subjects and the results of each of the evaluations will be entered separately. Each record corresponding to an evaluation, after approval by the researcher responsible, will be stored such that further editing cannot be performed. A backup copy of the database will be encrypted in a 512 bit system and uploaded weekly by safe transmission system to a web server. The study controller will store on the central computer the data obtained from each of the participating healthcare centres and will include all the records in the central database. Similarly, the study controller will make a weekly printout of the updated tables from each of the healthcare centres; these documents will be stored securely and kept as an original record for purposes of inspection or auditing or in case of loss of digital data. Each PDA will be the responsibility of the corresponding researcher at each health centre.

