### Data analysis

To describe the different baseline characteristics of the patients, we shall use measures both of position (the mean or the median, according to the asymmetry) and of variability (standard deviation or interquartile range) for the continuous variables, while the others will be described via their frequency distributions, comparing the experimental and control groups. Moreover, a graphic analysis will be made, using smoothed versions of the histograms, boxes and other representations.

For the principal result variable, the difference between the final value and the baseline Constant SFA score, measured in absolute terms, the experimental and control groups will be compared after adjusting by the baseline value and subsequently by other possible confounders. This analysis will be repeated in the follow ups at 3, 6 and 12 months. We will evaluate the effect of possible points of influence by repeating the model after exclusion of the observations with a large Cook-distance value. The assumptions of the model will be tested and reanalysed using a Q-Q plot diagram for the assumption of normality, and by comparing the studentised residuals versus the values of the independent variable for the assumption of constant variances.

For the secondary result variables, the bivariate analysis will be performed using contingency tables analysed by ji-squared tests (for tables larger than 2 × 2), by ji-squared tests corrected for continuity, or Fisher's exact test (for 2 × 2 tables), for the categoric variables, and by simple linear regression for all other cases. Two-dimensional graphs will also be used.

The multivariate analysis will depend on the nature of the response variable. When this is dichotomic, a binary logistic regression analysis will be made, and for this purpose we will establish the dummy variables needed for the categoric predictors. The inclusion of the "experimental group" or "control group" variable will be forced. The "forward procedure" method will be used to select the possible confounding variables in the model, and the entry criterion used will be the change in the likelihood ratio. The functional form of the continuous predictors will be studied via the corresponding statistical criteria, these being mainly graphic procedures.

For continuous variables, a multiple linear regression model will be used, and the same model-selection criteria and diagnostic procedures as described above will be applied.

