The placebo selected differs considerably from the acupuncture technique under study, but the intervention in itself is, in fact, difficult to disguise [27]. The depth of needle insertion and the manipulations subsequently effected prevent the use of placebos that are totally credible [28]. This is why we decided to apply an inactive control treatment (the TENS placebo), in order to subject the two groups of patients to the same rhythm of intervention. Nevertheless, the degree of credibility of the intervention and of the placebo will be assessed at the start and at the end of the study. This type of control was first used experimentally by Macdonald [29]. The placebo effect is related to the patient's expectation, to the observer and to the doctor's attention, in combination with classical Pavlovian-type response conditioning activated by the positive or negative expectation of a cure. Petrie and Hazleman [30]used a scale to measure the credibility of acupuncture treatment and that of the TENS placebo, and reached the conclusion that both methods were equally credible, thus justifying the use of the TENS placebo as a control.

Although the characteristics of the intervention prevent us from establishing a double blind design, we intend to blind the patients from the evaluator, and believe this simple blinding will make it possible to achieve sufficient control of possible bias.

As with any other multicentre study, we are confronted with certain disadvantages, such as the loss of unity of judgement, with the participation of various researchers, or the reduced homogeneity of the sample group and the parallel increase in data dispersion. In order to overcome these problems, we have had to create very simple criteria for patient selection, to avoid possible subjectivity as concerns the different researchers. Additionally, we have laid great stress on the need to obtain a good level of communication between the different work groups, a condition that is sometimes essential to standardise criteria and to guarantee the internal validity of the study. The best way to achieve this communication is by means of frequent meetings, the coordination of which will be the responsibility of the study controller.

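### Patients are randomised within each centre, but nothing in the planned primary analysis ensures that centre is in the model

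*Protocol article*

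**What the plan says.** **Allocation.** The Randomisation section states: "Randomisation will be carried out in each digital data recording system". It adds: "Every healthcare centre participating in the study has a specially-designed DDR based on a Dell Axim × 30 PDA". The patient is the unit allocated, and the allocation runs separately in each centre. The article does not say whether the sequence in a device is blocked or simple.

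**Evaluator.** Under Data collection and analysis, access to each device is limited to three users: "1) the healthcare centre evaluator; 2) the doctor applying the treatments; 3) the study controller". Evaluator and treating doctor therefore go with centre.

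**Primary analysis.** Under Data analysis, the outcome is the change in SFA score, and "the experimental and control groups will be compared after adjusting by the baseline value and subsequently by other possible confounders". The confounders are not named, and centre is not mentioned. Later in that section, in the paragraph on binary outcomes, treatment group is the one term that must be included, and "The 'forward procedure' method will be used to select the possible confounding variables in the model". For continuous variables, "the same model-selection criteria and diagnostic procedures as described above will be applied".

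**Centre differences.** The Discussion lists among the drawbacks of a multicentre study "the reduced homogeneity of the sample group and the parallel increase in data dispersion". It answers with simple selection criteria and regular meetings. No analysis step is offered.

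**The concern.** Centre is known for every patient before allocation and is the level within which the trial randomises. Most of the SFA scale (65 of 100 points, under Main result variable) consists of objective elements, including goniometer readings and weight raised in abduction, which the evaluator scores. The authors themselves expect judgement and samples to differ between centres. A design feature of this kind belongs in the primary model by prior decision. As written, it may be omitted, or it may enter through an unspecified choice of confounders.

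Precision is what is at stake. Any between-centre variation in SFA change that baseline SFA does not explain stays in the residual. If allocation is balanced within each device, the standard error from a model without centre is also somewhat too large for the design. Under simple allocation that standard error is valid, but chance imbalance between arms within centres is not removed.

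**Working it through.** **Inputs from Sample size and associated power:** means 70 and 65 (difference 5), SDs 17 and 18, two-sided alpha 0.05, power 0.80, and 188 + 199 = 387 evaluable patients. **Not in the document, so assumed:** ICC from 0 to 0.10; 5 or 10 centres of equal size for the simulation.

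**1. Reproducing the plan's figure.** With allocation proportional to the SDs, n₁ = s₁(s₁+s₂)(z₀.₉₇₅+z₀.₈₀)²/d² and n₂ = s₂(s₁+s₂)(z₀.₉₇₅+z₀.₈₀)²/d². With (1.960+0.842)² ≈ 7.849:
- n₁ = 17 × 35 × 7.849/25 = 186.8
- n₂ = 18 × 35 × 7.849/25 = 197.8

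With the t distribution, 188 and 199 give power 0.8005. The stated figures reproduce and are not in dispute here.

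**2. Effect of centre on power.** Power = Φ(5/SE − 1.96), where SE² = 17²/188 + 18²/199 = 1.537 + 1.628 = 3.165. So SE = 1.779 and power = Φ(0.850) = 0.802.

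(a) If the SDs of 17 and 18 already contain between-centre variation, fitting centre multiplies SE² by (1 − ICC). (b) If they are within-centre SDs, omitting centre divides SE² by (1 − ICC).

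| Assumed ICC | (a) power with centre fitted | (b) power with centre omitted | (b) N then needed, 387/(1 − ICC) |
|---|---|---|---|
| 0 | 0.802 | 0.802 | 387 |
| 0.02 | 0.810 | 0.794 | 395 |
| 0.05 | 0.822 | 0.782 | 407 |
| 0.10 | 0.842 | 0.760 | 430 |

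**3. Simulation check.** There were 3,000 trials per scenario, with SD 17.5, difference 5, and 5 centres of 77 or 10 centres of 38. No baseline covariate was included. Monte Carlo error is about 0.004 for type I error (√(0.05 × 0.95/3000)) and 0.007 for power (√(0.8 × 0.2/3000)).

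| ICC | Allocation in centre | Centres | Power, omitted | Power, fitted | Type I error, omitted |
|---|---|---|---|---|---|
| 0.05 | balanced | 5 | 0.806 | 0.818 | 0.051 |
| 0.05 | balanced | 10 | 0.805 | 0.818 | 0.045 |
| 0.05 | simple | 5 | 0.793 | 0.804 | 0.047 |
| 0.05 | simple | 10 | 0.793 | 0.800 | 0.052 |
| 0.10 | balanced | 5 | 0.827 | 0.847 | 0.044 |
| 0.10 | balanced | 10 | 0.803 | 0.829 | 0.041 |
| 0.10 | simple | 5 | 0.796 | 0.823 | 0.052 |
| 0.10 | simple | 10 | 0.792 | 0.823 | 0.044 |

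Type I error is not inflated in any of these scenarios. Under balanced allocation at ICC 0.10 it falls slightly below 0.05. Gains are 0.6 to 1.3 points at ICC 0.05 and 2.0 to 3.1 points at 0.10, somewhat less than the formula's 2.0 and 4.0. At ICC 0 the change was nil under balanced allocation, and a loss of 0.4 points (5 centres) or 1.1 points (10 centres) under simple allocation.

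**4. Limit of the arithmetic.** The SDs of 17 and 18 describe final scores. The planned model adjusts for baseline, so the relevant ICC is that of the baseline-adjusted outcome. The figures show direction and order of size; they are not the power of the planned analysis.

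**The case against.** The strongest objection is that this is silence. The phrase about other possible confounders is open, no sentence excludes centre, and covariate lists are commonly left to an analysis plan. In part that stands: centre could still be added. But the article does fix an adjustment rule, names baseline SFA and not centre, and itself expects dispersion between centres. Naming centre is a concrete change to that rule.

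A second objection is that the outcome is change from baseline, adjusted for baseline. If one evaluator scores a patient at both visits, a stable scoring shift is partly removed already. This stands, and it is why only the unabsorbed part of the between-centre variation counts.

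A reader might infer more than the document supports:
- **That centre is the unit of randomisation.** The patient is; centre acts at most as a stratum.
- **That the recorded baseline variables are the pool of confounders and so shut centre out.** No section says so, and data are collected by centre.
- **That forward selection certainly governs the primary model.** It is described after the secondary-variable paragraph, and its reach back to the primary comparison is unclear.
- **That the standard error is wrong for the design.** This needs balance within each device, which is not stated.
- **That adding centre makes good the power lost through the dropout allowance.** A 20% loss from 226 and 239 leaves about 181 and 191. The same formula gives 78.7%, rising to 79.5%, 80.7% or 82.8% at ICC 0.02, 0.05 or 0.10. But this uses unadjusted final-score SDs. With an assumed baseline correlation of 0.3 or 0.5, SE² is multiplied by 0.91 or 0.75, and power is about 82% or 89% without centre. The 78.7% is therefore not the planned analysis's power.

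**Conclusion.** The point holds as a matter of precision. Allocation and evaluator both go with centre, the authors expect centres to differ, and nothing ensures that centre is in the primary model. There is no bias and no inflation of type I error. The cost of omission is residual variance that could have been removed, and a slightly conservative test if allocation within devices is balanced.

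On the planned SDs, the illustrative gain at 387 evaluable patients is from about 80% power to 81%, 82% or 84% at an assumed ICC of 0.02, 0.05 or 0.10; simulation suggests somewhat less. At an ICC of 0 there is essentially nothing to gain. Neither the ICC of the baseline-adjusted outcome nor the number of centres is given, so the size for this trial is unknown. This is a free improvement and not a threat to the trial's conclusions.

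**What to change.** In Data analysis, state the primary model as SFA change regressed on treatment, baseline SFA and centre, with centre forced in and not left to any selection step. If some centres are very small, use a random intercept for centre, and make that decision before unblinding. Use the same terms at the 3-month assessment (T-2) and for the continuous secondary outcomes.

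No new data or patients are needed, because records already arrive by centre. The cost is one degree of freedom per centre beyond the first as a fixed effect, which is few against 387 evaluable patients. The worst case simulated (10 centres, simple allocation, no centre effect at all) lost about one point of power.
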